## Abstract

**Background:**

Autism Spectrum Disorder (ASD) is a neurodevelopmental disorder characterised by persistent deficits in social communication and the presence of restricted, repetitive behaviours or interests. Previous literature has identified a link between the gut and ASD; however, the underlying mechanisms remain unclear. Gut microbiota dysbiosis has been extensively reported in cohort studies of ASD, and specific microbial metabolites or by-products may serve as potential biomarkers for ASD. Additionally, children with ASD often exhibit food refusal, have a limited food repertoire and display a tendency to consume the same foods frequently; thus, these behaviours increase their risk of malnutrition (over-nutrition or under-nutrition) compared to typically developing (TD) healthy children. This study primarily aims to identify oral and gut microbiota among children with ASD and TD healthy children. The secondary aim is to determine the associations between oral and gut microbiota with nutritional status among children with ASD. The findings will enhance understanding of the aetiology of ASD and inform early intervention strategies to mitigate disease severity and early identification of malnutrition in genetically at-risk children.

**Methods and analysis:**

This observational, age-matched, case-control study is conducted in Malaysia among 40 male children with ASD and age-matched with 40 TD healthy controls aged 4–10 years. The dependent variables include the microbiota profile, identified through metagenomic sequencing analysis of saliva and faecal samples, and autism severity, assessed through validated questionnaires. Independent variables include nutritional status, determined through Subjective Global Nutrition Assessment (SGNA), anthropometry and dietary measurements, gastrointestinal symptoms, eating behaviour, behavioural profile, and sleep quality. Data collection is expected to be completed by June 2026. The study nature may limit causality establishment. Analyses will use chi-square/ANOVA for group comparisons, SparCC for microbiota correlations, and mixed-effects logistic regression to model associations.

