### Sample size

This study aims to compare the microbial community structure between the ASD and TD healthy groups and within the groups, generating plausible distances relevant to the study objectives. Beta diversity is used to estimate the sample size or statistical power for this study. The recommended sample size is 60 participants, determined based on calculations using data from a study conducted by Li et al. [31]. Due to the limited availability of similar studies, this prior research served as a reference to obtain appropriate variance estimates [31]. The total study sample size of 60 participants has been adjusted to account for a possible 30% dropout rate; thus, this study aims to recruit 80 participants (40 children with ASD and 40 TD healthy children). The primary outcomes are microbial beta diversity and nutritional status. Secondary microbiota comparisons will be adjusted for multiple testing using the Benjamini-Hochberg false discovery rate, and post-hoc power analyses will be conducted to assess adequacy for multivariate models.

The study included only male children to eliminate potential gender bias, as the male predominance in ASD has been well-documented in epidemiological studies and widely recognised in the field [32–34]. This approach also ensures greater homogeneity in the demographic and microbiome datasets, thereby enhancing the precision and reliability of the findings.

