### Nutritional status and dietary assessment

A Subjective Global Nutrition Assessment (SGNA) will be utilised to determine the nutritional status of the children [49]. SGNA evaluates nutritional status in two main categories: Nutrition Focused Medical History (NFMH) and Physical Exam (PE). NFMH includes evaluating the appropriateness of current height and weight for age, changes in body weight, dietary adequacy, gastrointestinal symptoms, functional capacity, and metabolic aspects of disease. PE evaluates subcutaneous fat loss, muscle wasting, and nutrition-related oedema. The combined NFMH and PE evaluation will generate an overall SGNA ranking of normal/well-nourished, moderately malnourished, severely malnourished [49].

Dietary intake of the children will be obtained through parental interviews, using 3-day dietary recalls (two weekdays and one weekend day). To assist with the food intake portion size estimation, pictures of household measuring tools will be provided. Detailed information about the food and beverages consumed, such as cooking methods and brand names (if applicable), will be recorded. Nutrient analysis will be generated using the Nutritionist Pro^TM^ Diet Analysis software (Axxya Systems LLC, USA) and the Malaysian Food Composition Database (MyFCD). Nutrient adequacy will be assessed by comparing the intake to the Malaysian Recommended Nutrient Intakes (RNIs) [50]. Adequate intake will be defined as meeting or exceeding 100% of the RNI for macro- and micronutrients Portion size estimation in dietary assessment has been validated as reliable [51]. As dietary data will be parent-reported, research assistant will verify accuracy by reconfirming food intake during data entry prior to nutrient analysis. Basal metabolic rate (BMR) will also be calculated to identify potential underreporting or overreporting of energy intake.

Anthropometric measurements will be conducted by trained research assistant ([name]), a registered dietitian who completed standardized anthropometric assessment training measurement according to the standardized guideline by ISAK [52]. Observer and assessor training will be provided to research staff while obtaining data on 3-days dietary recall, with peer review and error checks to ensure data reliability.

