### Statistical analysis plan

Data analysis will be conducted using R software and its available packages. The differences in microbiota profiles, socio-demographic factors, emotional and eating behaviour, and nutritional status between children with ASD and TD children will be compared using the chi-square/Fisher’s exact test and ANOVA where appropriate. Student’s t-test will be applied to compare BMI and age between groups. Pre-filtering and inference of correlations will be performed using the Sparse Correlations for Compositional Data (SparCC) correlation metric [66], with a minimum R-value threshold of 0.35. SparCC will be used to correlate salivary and faecal bacterial markers detected in saliva and faecal samples from the same child. The associations between microbiota profiles, socio-demographic factors, emotional and eating behaviour, autism severity, sleep quality, gastrointestinal symptoms, and nutritional status among children with ASD will be modelled using mixed-effects logistic regression (MELR) model and random forest. Normality, linearity, homoscedasticity, and multi-collinearity will be assessed to ensure that the assumptions of regression models are met. Potential confounders, including age, and socioeconomic status will be adjusted for fixed effects. Model assumptions will be performed using DHARMa package in R to assess dispersion, zero-inflation and overall fit [67]. In case of heteroscedasticity or overdispersion, corrective strategies will include the use of an observation-level random effect, modelling dispersion or zero-inflation with glmmTMB [68], or applying bias-reduced logistic regression (Firth correction) [69] or bootstrap inference to mitigate small-sample bias [70]. Study results are expected in December 2026.

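### No test that uses order is named for the three-level SGNA ranking, one measure of a stated primary outcome; the power cost depends on how many children are severe

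*Protocol article*

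**What the plan says.** The Sample size section states: "The primary outcomes are microbial beta diversity and nutritional status". The section on nutritional status and dietary assessment says: "A Subjective Global Nutrition Assessment (SGNA) will be utilised to determine the nutritional status of the children", and the result is an "overall SGNA ranking of normal/well-nourished, moderately malnourished, severely malnourished". That is a three-level scale with a clear order. Anthropometric z-scores and dietary intake are measured as well.

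The Statistical analysis plan section puts nutritional status in one list with microbiota, socio-demographic and behavioural variables. It says that the list "will be compared using the chi-square/Fisher’s exact test and ANOVA where appropriate". Student's t-test is named separately for BMI and age. The abstract gives the shorter version: "Analyses will use chi-square/ANOVA for group comparisons". No rank test, trend test or ordinal model appears for any comparison of the two groups.

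**The concern.** SGNA is a category, so chi-square or Fisher is the test that a reader would expect from that list. Both treat the three levels as unordered. The p-value stays the same if the levels are relabelled in any order, so the test spends power on patterns that do not mean worse nutrition. Nor does a 2 x 3 table supply one odds ratio with a confidence interval.

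At stake is the chance of detecting a consistent shift towards malnutrition on a measure of a stated primary outcome. The sample size was derived from beta diversity alone, so nothing shows that this comparison has power to spare.

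**Working it through.** **Inputs from the article.** Three SGNA levels; "The recommended sample size is 60 participants", taken here as 30 per group; 40 + 40 recruited; 30% dropout. The article gives no power figure for SGNA, so there is none to reproduce. Applying the stated dropout to the recruited number gives 80 × 0.70 = 56, or 28 per group. The range of interest is therefore 28 to 40 per group.

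**Assumed inputs.** A two-sided 5% level, and SGNA shares written as well-nourished/moderate/severe in percent. The article supplies neither.

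**Step 1: value of the order in large samples.** If a 1-df ordered test captures the whole difference, it and the 2-df chi-square share a non-centrality λ. Power is P(χ²(df, λ) > c), with c = 3.84 for 1 df and 5.99 for 2 df.

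| λ | 1-df power | 2-df power | Loss (points) |
|---|---|---|---|
| 2.06 | 30% | 23.1% | 6.9 |
| 3.84 | 50% | 40.1% | 9.9 |
| 4.90 | 60% | 49.5% | 10.5 |
| 7.85 | 80% | 70.9% | 9.1 |
| 10.51 | 90% | 83.5% | 6.5 |

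**Step 2: simulated 2 x 3 tables** (100,000 per row; 4,000 for Fisher). Gains were taken before rounding.

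| ASD vs TD | n per group | Chi-square | Fisher | Wilcoxon | Wilcoxon minus chi-square |
|---|---|---|---|---|---|
| 60/30/10 vs 85/12/3 | 40 | 61.4% | 62.1% | 72.7% | +11.4 |
| same | 30 | 48.0% | 50.0% | 60.0% | +11.9 |
| 70/25/5 vs 90/9/1 | 40 | 49.7% | 52.7% | 63.3% | +13.7 |
| same | 30 | 37.8% | 38.9% | 50.9% | +13.2 |
| 70/28/2 vs 90/9/1 (severe rare) | 40 | 55.0% | 56.5% | 62.2% | +7.3 |
| same | 30 | 43.6% | 40.9% | 49.7% | +6.1 |
| 80/20/0 vs 95/5/0 (none severe) | 40 | 57.4% | 41.6% | 57.4% | 0.0 |
| 60/38/2 vs 80/10/10 (non-monotone) | 40 | 84.0% | 83.1% | 35.7% | −48.3 |

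At 28 per group, 60/30/10 vs 85/12/3 gives 44.6% for chi-square against 56.9% for Wilcoxon (+12.3), and 70/25/5 vs 90/9/1 gives 34.5% against 48.3% (+13.8). With severe very rare (75/24/1 vs 92/7.5/0.5) the gain is about 4 to 5 points.

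**Step 3: how much of this comes from order?** With equal shares of 85/12/3 in both groups, the rejection rate was 3.3 to 3.8% for chi-square, 2.3 to 3.6% for Fisher and 4.4 to 5.3% for Wilcoxon. The tests therefore do not run at the same actual size. The row with no severe child shows the effect plainly. The table is then 2 x 2, order carries no information, and Fisher still falls 15.8 points behind. Like for like, an exact ordered test differs from Fisher by about −2 to +8 points. The upper end occurs when severe is populated, and the lower end when it is rare.

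**The case against.** **The mapping is an inference.** A reader might infer that the plan commits SGNA to chi-square or Fisher. It does not: the sentence covers several variables, leaves the choice to what is appropriate, and ANOVA on scored levels would use the order. Matching each test to each variable is also commonly left to a full analysis plan. This stands as a limit. Still, the section does name the tests for nutritional status, none is an ordinal method, and no scores for ANOVA are given.

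**The role of nutritional status is unsettled.** The abstract says "Independent variables include nutritional status, determined through Subjective Global Nutrition Assessment (SGNA" and places it in a secondary aim among children with ASD. SGNA is also only one of several nutritional measures. This too stands, but the comparison between groups is planned either way.

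**The contrast may be small.** The Background cites 9.3% and 15% underweight in two Malaysian ASD samples. These are not SGNA results, but they suggest modest shifts. With 91/8/1 vs 96/3.5/0.5, power is 7% for chi-square against 10% for Wilcoxon at 28 per group, and 12% against 16% at 40. Either test is then badly underpowered.

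**Direction.** A reader might infer that a significant chi-square leaves the direction unknown. That is true of the p-value only; the group proportions would show it. What is missing is a single estimate with an interval.

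**The ordered test can lose.** It loses heavily under a non-monotone difference. The example above needs healthy controls to be severely malnourished more often than boys with ASD, which runs against the malnutrition risk that the abstract describes.

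**Conclusion.** The point holds in a conditional form. The named tests include no ordinal method for an ordered three-level ranking that measures a stated primary outcome, and on the natural reading the order is ignored.

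For same-direction shifts at 28 to 40 per group and an assumed two-sided 5% level, a tie-corrected Wilcoxon test gains over chi-square 0 points with no severe child, about 4 to 7 with severe rare (3 to 4 if the contrast is also small), and up to about 14 with severe populated. A reader might take one fixed loss, such as 7 to 12 points, from the mid-range scenarios. The article does not support that, because it gives neither the SGNA distribution nor the significance level, and part of the gain is the conservatism of the nominal tests. When severe is rare, an exact ordered test gains little or nothing over Fisher. The lasting benefits are a test aimed at a shift in nutrition and one interpretable estimate.

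**What to change.** In the Statistical analysis plan section, and briefly in the abstract, state that the three-level SGNA ranking is compared between ASD and TD with a tie-corrected Wilcoxon or linear-by-linear trend test. Add a proportional-odds model with age as covariate, given the age matching, to give one odds ratio and 95% CI. Report the proportion at each level by group, and note that the analysis becomes a two-level comparison if no child is severe. Keep chi-square or Fisher for unordered categories such as ethnicity and occupation.

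This costs a sentence or two and no new data, and should be fixed before results are seen. There are two downsides: the odds ratio assumes a similar shift at both cut points, and an ordered test loses power if the difference is non-monotone.

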**Conclusion:**

This study advances understanding of ASD-related microbiota, guiding personalised nutrition and precision healthcare in Malaysia.

## Background

Autism Spectrum Disorder (ASD) has both genetic and environmental origins [1]. Research has consistently shown that common and rare inherited variations (heritability) play a role in the genetic origins of ASD [1]. A multinational cohort study estimated the heritability of ASD to be approximately 80%, with modest differences in the sources of ASD risk across children from Denmark, Finland, Sweden, Israel, and Western Australia [1]. Moreover, the UK population-based twin cohort study reported ASD heritability estimates ranging from approximately 56% to 95% [2]. Nevertheless, debates persist regarding the relative importance of environmental factors compared to genetic predisposition in ASD [3]. Shared environmental effects refer to environmental factors common to individuals within a family or community, such as parenting practices, social and cultural influences, and exposure to toxins or pollution [4]. Recent research has identified that shared environmental effects can account for up to 50% of the variance in ASD risk in twin studies [5,6]. Furthermore, a recent meta-analysis research highlighted specific environmental factors that may contribute to ASD development, including prenatal exposure to toxins such as pesticides and air pollution, maternal stress during pregnancy, and early childhood experiences such as poor nutrition, neglect, and abuse [7]. These findings suggest that shared environmental factors may hold comparable significance to genetic factors in the development of ASD.

Children with ASD are frequently associated with disruptive mealtime behaviours, such as severe food refusal, a limited food repertoire, and high-frequency single-food intake [8]. These behaviours are closely related to sensory processing difficulties, such as aversion to specific textures, smells, and tastes [9]. Consequently, children with ASD are at an elevated risk of poor nutritional status. A local study conducted among 224 children with ASD in Kuala Lumpur reported that the prevalence of underweight, stunting, wasting/thinness and overweight/obesity were 9.3%, 8.0%, 4.0%, and 21.5%, respectively [10]. Another recent study in central region of Malaysia (Selangor, Kuala Lumpur, and Negeri Sembilan) involving a total sample size of 150 children with ASD documented that 15% of the children were underweight, and 52% were overweight and obese [11]. Although most children had adequate total energy and protein intakes, their fat intake exceeded the recommended levels [10]. Moreover, the majority of the children did not meet the Recommended Nutrient Intake (RNI) requirements for several key nutrients, including fibre (99.6%), thiamine (67.4%), vitamin C (50.9%), vitamin D (98.2%), vitamin E (74.6%), vitamin B12 (64.3%), folate (88.8%), calcium (90.2%), and zinc (77.2%) [10]. Therefore, a comprehensive understanding of the nutritional risks faced by children with ASD is essential for healthcare professionals to develop effective, targeted nutritional interventions.

Research has shown that children with ASD may exhibit altered nutrient metabolism, including deficiencies in essentials vitamins and minerals, which could contribute to the development and progression of the disorder. For example, studies have reported lower levels of vitamins B6 and B12 in children with ASD, both of are critical for neurological function [12–14]. Dietary habits are considered one of the main factors influencing the diversity of human gut microbiota [15]. Furthermore, host genetics, dietary habits, gut physiology, hygiene level, stress, and physical activity influence the gut microbiota. The human gut “metagenome” is a complex consortium of trillions of microbes, whose collective genomes contain over 100 times as many genes as the human eukaryote genome [16]. This essential “organ,” the microbiome, provides the host with protection against pathogens, enhancement of immune system and metabolic capabilities, as well as modulation of gastrointestinal (GI) development [17].

### Review of previous literature

The gut-brain axis is bidirectional, with signals from the brain also influencing gastrointestinal physiology and microbial composition through immune, endocrine and neural pathways [18,19]. Emerging evidence also suggested that the gut microbiome may play a role in the development and function of the brain, with some studies suggesting that alterations in the microbiome may contribute to ASD symptoms. For example, gut bacteria are capable of producing neurotransmitters such as serotonin and dopamine, which are critical regulators of mood and behaviour [20–22]. While some studies have reported consistent differences in the faecal microbiota of children with ASD [23,24], others have found no significant differences or have presented conflicting results [25]. The alterations in microbial composition have been linked to functional changes in brain activity and ASD-related symptoms, with studies implicating Clostridium overgrowth, inflammation, and disrupted neurotransmitter metabolism [18,19,26,29]. Studies have found that children with ASD have lower levels of *Bifidobacterium* and *Lactobacillus*, bacteria typically considered beneficial, and higher levels of *Clostridia* and *Desulfovibrio*, which are often associated with inflammation and gastrointestinal disturbances [26–29].

These findings have led to speculation that imbalances in the gut microbiome could contribute to the development or severity of ASD, potentially through mechanisms involving inflammation, immune dysregulation, or altered communication between the gut and brain (the gut-brain axis). While the relationship between nutrition, the microbiome, and ASD is still not fully understood, there is growing evidence suggesting that interventions targeting these factors may be beneficial in the managing ASD symptoms.

This study aims to address the knowledge gap by exploring the potential association between microbiota profiles, nutritional status and autism severity in children with ASD. Previous research has highlighted the potential role of gut microbiota imbalances, nutritional deficiencies, and their contribution to ASD progression [10,12–14,18,19,26–29]. However, there remains a lack of understanding of these relationships in Southeast Asia, particularly in Malaysia, where cultural and dietary practices may influence these factors differently from Western populations. This research is among the first comprehensive studies in Malaysia to simultaneously examine microbiota profile alongside nutritional status, particularly BMI and ASD severity. Existing studies have not fully integrated these components, often focusing solely on microbial diversity or gastrointestinal symptoms. The inclusion of nutritional status and a thorough analysis of dietary factors influenced by Malaysian culture are strengths of this study. The main strength of this research is its case-control study design, enabling the identification of specific microbiota and nutritional patterns associated with ASD severity as compared to TD healthy controls. By providing baseline data specific to the Malaysian context, this research aims to address the limited studies on the nutritional and microbiome profiles of children with ASD in Southeast Asia. With additional independent variables such as eating behaviour, behavioural profile, and sleep quality, the findings from this study could guide the development of targeted interventions, such as dietary modification or medical management, tailored to the unique needs of Malaysian children with ASD, ultimately enhancing their health and well-being.

### Objectives

This study primarily aims to understand the role of oral and gut microbiota in the molecular mechanisms underlying the aetiology of ASD among children in Malaysia. Specifically, this study aims to determine whether there is an association between the oral and gut microbiota and socio-demographic factors, nutritional status, and autism severity among children with ASD compared to TD healthy children. Additionally, this study also measures additional independent variables to determine the associations between oral and gut microbiota and gastrointestinal symptoms, eating behaviour, behavioural profiles and sleep quality.

The hypothesized relationships between gut microbiota, nutritional status, dietary intake, and ASD severity are illustrated in Fig 1.

